### Sample Size

#### Primary Outcome Measurement

Our intervention targets products that collectively account for 87% of free sugars from all product purchases in remote communities. The effects of the strategy are likely to be seen from the beginning of the intervention period, and we expect that sales (gram weight) of targeted products will be reduced by approximately 10% and free sugars (g/MJ) by approximately 8% to 9% throughout the intervention; we will test if this is sustained postintervention. A mean effect size of a 10% reduction in targeted discretionary product categories purchased is based on Batis et al (2016) [39], where an 8% tax applied by the Mexican government on nonessential energy-dense foods resulted in low socioeconomic status households purchasing on average 10.2% less taxed foods than expected (−44 [−72, −16] g per capita per month). Using 20 weeks of data for 20 remote stores (SHOP@RIC data), we found a 95% CI for the relative change of free sugars (g/MJ) for 2 randomly chosen groups of 10 stores to have width ±3.6% approximately. This anticipated precision is excellent for detecting an anticipated effect of the primary outcome of approximately 8% to 9%. A corresponding power calculation is not necessary [40]; however, the proposed study would likely have approximately 90% power to detect a 6% reduction in the primary outcome (free sugars g/MJ).

##### Customer Response

Under the assumption of an intracluster correlation equal to 0.01 and a cluster size equal to 45 (on the basis of 24 communities), we calculated a sample size allowing a study design of 1.4. With a sample of 1080 customers, and assuming a relative SD of 40% for the outcome discretionary product dollars of total dollars, the study will have 80% power to detect an 8% difference (from 50% in the control group to 42% in the intervention group) in the discretionary product dollars and total dollars at an alpha of .05.

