### Customer Intercept Survey Substudy

In the final 2 weeks of the intervention, we will conduct customer intercept surveys (1080 unique customers; 45 per store) from control and intervention stores to identify the following:

Differences among customers in discretionary food and drink purchasing in intervention and control communities.Customer characteristics that predict discretionary product purchases.Proportion of customers who regularly purchase food and drinks from other food outlets in or outside of the community.

Using a structured close-ended question survey in electronic format (iSurvey) with standardized scripts, trained surveyors with support from store staff will interview customers after they complete their purchase. Surveyors will be scheduled to survey customers at store front (postshop) over a period of 6 hours (3×2 hour sessions over the course of the day) per day for up to 3 days, to capture a broad spectrum of customers and shopping purpose, planned or unplanned, each subject to different levels of impulse shopping propensity. We consulted with ALPA to ensure this is feasible on the basis of number of transactions per day. We anticipate surveys to take 5 to 10 min per customer.

Upon exiting the store, customers will be invited to provide their receipt (a photograph of the receipt will be recorded) and respond to a short-item questionnaire to gather information on characteristics of the customer (age range, gender, shopping alone versus with child or others, and impulse shopping propensity). Data on payment method (eg, cash or card) and food shopping frequency at other retail outlets will also be collected.

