## Results

As of August 2018, 20 stores consented to participate and were randomized to receive the intervention or continue usual practice. The 12-week strategy ended in December 2018. The 24-week postintervention follow-up will occur in May 2019. Results are expected for 2019.

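### The customer survey's 1080 customers and 80% power assume 24 communities, but only 20 stores were randomized; at 45 per store that is 900 customers and about 70.5–72% power by the plan's own method

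*Protocol article*

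**What the plan says.** The sizing is in the protocol article under Sample Size, Customer Response. Its inputs are:

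- "Under the assumption of an intracluster correlation equal to 0.01";
- "a cluster size equal to 45 (on the basis of 24 communities";
- a design effect, printed as "we calculated a sample size allowing a study design of 1.4";
- a total of 1080 customers;
- a spread described as "assuming a relative SD of 40% for the outcome discretionary product dollars of total dollars".

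From these it states 80% power, at alpha .05, to detect a fall in the discretionary share of spending from 50% to 42%.

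The Customer Intercept Survey Substudy section repeats the target: "we will conduct customer intercept surveys (1080 unique customers; 45 per store) from control and intervention stores". It places the survey in the final 2 weeks of the intervention.

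The Results section says "As of August 2018, 20 stores consented to participate and were randomized to receive the intervention or continue usual practice", and the Abstract says the same. The Recruitment of Stores section explains where 24 comes from: when the study was designed, the retail partner managed 25 stores in 24 communities. One community has two of those stores, and both go to the same arm.

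**The concern.** Three figures in the current text cannot all hold: 1080 customers, 45 per store, and 20 randomized stores. The survey draws on control and intervention stores after randomization, so at most 20 stores can supply customers. Either the total is lower than 1080 or the number per store is higher than 45. In both cases there are fewer clusters than the power calculation used.

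Two things are at stake. A reader cannot tell which recruitment target applied. The 80% power for the intervention-versus-control contrast, which the Customer-Level Response (Substudy) section plans to estimate, is also more than the randomized design provides at 45 per store.

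**Working it through.** **Inputs from the Customer Response paragraph.** ICC 0.01; cluster size m = 45; 24 communities; N = 1080; 50% versus 42%; alpha .05; design effect 1.4. The Design section gives 1:1 allocation.

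**Assumptions needed.** The test is two-sided (sidedness is not stated). The SD is 40 percentage points, so the standardized difference is 8/40 = 0.20.

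**Formulas.**

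- Design effect: DE = 1 + (m − 1) × ICC
- Effective number per arm: n = (N/2)/DE
- Noncentrality: λ = 0.20 × √(n/2)
- Power (normal) = Φ(λ − 1.96)
- Difference detectable with 80% power = (1.96 + 0.84) × 40 × √(2/n)

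**Step 1: reproduce the plan's figure (24 × 45 = 1080).**

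- DE = 1 + 44 × 0.01 = 1.44, printed as 1.4.
- DE 1.44: n = 540/1.44 = 375; λ = 0.20 × √187.5 = 2.739; power = 78.2%.
- DE 1.4: n = 540/1.4 = 385.7; power = 79.3%.
- In reverse, 80% power needs 393 per arm before clustering, and 2 × 393 × 1.4 = 1100, within 3% of 1080.

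The normal method with an SD of 40 points therefore reproduces the stated 80%. Other readings of the 50% versus 42% contrast do not: SD of 20 points (40% of a mean of 50%) gives over 99.9%, a one-sided test gives 86%, and a comparison of two proportions gives 59–61%.

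**Step 2: same method with 20 stores (20 × 45 = 900).**

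- DE 1.44: n = 450/1.44 = 312.5; λ = 0.20 × √156.25 = 2.50; power = 70.5%.
- DE 1.4: n = 450/1.4 = 321.4; power = 71.8%.
- Detectable difference (DE 1.44): about 8.2 points at 1080 and 9.0 points at 900.

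**Step 3: variants.** All rows use DE from the formula. The t column uses a noncentral t with clusters minus 2 degrees of freedom.

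| Design | Customers | DE | Power, normal | Power, t |
|---|---|---|---|---|
| 24 clusters × 45 (planned) | 1080 | 1.44 | 78.2% | 74.5% |
| 20 clusters × 45 | 900 | 1.44 | 70.5% | 65.7% |
| 19 clusters × 45 | 855 | 1.44 | 68.3% | 63.2% |
| 20 clusters × 54 | 1080 | 1.53 | 75.7% | 71.0% |

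With DE 1.4, the t figures in the first two rows are 75.6% and 67.0%.

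The 19-cluster row applies if the two-store community is among the 20 stores and 45 customers are taken per community; it treats the arms as equal in size. The last row keeps 1080 by taking 1080/20 = 54 per store. This recovers part of the loss, because extra customers within a store do not fully replace lost clusters.

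**Sensitivity to the SD reading.** With an SD of 20 points and an 8-point difference, power exceeds 99% at both 1080 and 900. The stated 80% would then itself be unexplained. The conflict in the counts does not depend on the SD.

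**The case against.** The strongest defence is that nothing was miscalculated. The product 24 × 45 = 1080 is right, the stated power reproduces to within 2 points, and 24 was the number of communities available at the design stage. On this view the paragraph is a pre-recruitment assumption and the Results section merely reports what followed. That is right about the cause: this is a figure left unrevised after recruitment, not a slip in the arithmetic. It does not remove the conflict. The store count in Recruitment of Stores is dated to the design stage, but the survey target and the power claim are not. They are written as what the study will do, in an article that already reports 20 randomized stores.

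Three stronger readings are tempting but not supported:

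- **Power falls from 80% to 66%.** This compares a normal-based figure with one using a t reference that the plan's calculation does not appear to use. On the t reference the planned design had only about 75%. Like for like, the fall is from 78–79% to 70.5–72%, or from about 75% to 66–67%.
- **The survey had 900 customers.** The article does not report how many were surveyed. A total of 1080 at 54 per store remains possible.
- **The trial is underpowered.** The primary outcome comes from store sales data, and its precision calculation under Primary Outcome Measurement already uses two groups of 10 stores.

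It is also fair that the survey is a substudy in a convenience sample, and that the between-arm contrast is one of its three purposes. This limits the severity.

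**Conclusion.** The point holds at moderate severity. The stated survey size and power belong to a 24-community design, whereas 20 stores were randomized. At 45 per store that is 900 customers in at most 20 clusters, or 855 in 19 if the two-store community is included and 45 are taken per community.

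By the method that reproduces the plan's figure, power falls by about 8 percentage points, and the chance of missing an 8-point difference is nearly 30% rather than the stated 20%. The count mismatch is certain. The power figures are conditional on an SD of 40 percentage points, a two-sided test and the plan's ICC of 0.01. The consequence is confined to the survey's intervention-versus-control comparison.

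**What to change.** Reconcile the Customer Intercept Survey Substudy and Customer Response sections with the Results section:

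1. State how many stores and communities the survey covers, whether 45 applies per store or per community, and the customer total actually targeted.
2. State whether the SD of 40% is in percentage points or relative to the mean.
3. Restate power to match. If the SD is 40 points, this is about 70–72% at 45 per store, or 80% power for about 9 points. If 1080 was kept at 54 per store, it is about 76% with design effect 1.53. If a t reference is preferred, give the planned and revised figures on that same basis.

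By the article's timeline the sampling window had closed when the 12-week strategy ended in December 2018, so the survey contrast should be read from its confidence interval and not from planned power. The cost is wording only. No new data are needed, and the stated power becomes less favourable.

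### The survey power statement puts a relative SD beside an absolute difference: its printed inputs give over 99.9% power, not 80%, so the SD or the difference is off by a factor of two

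*Protocol article*

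**What the plan says.** The Customer Response part of Sample Size gives all the inputs in two sentences. Clustering is set by an "intracluster correlation equal to 0.01 and a cluster size equal to 45 (on the basis of 24 communities"). From this the authors write that "we calculated a sample size allowing a study design of 1.4", which is evidently the design effect.

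The power claim then starts "With a sample of 1080 customers". It continues "assuming a relative SD of 40% for the outcome discretionary product dollars of total dollars" and concludes that there is "80% power to detect an 8% difference (from 50% in the control group to 42% in the intervention group"), "at an alpha of .05".

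Two other sections matter. Design sets 1:1 allocation. Customer-Level Response (Substudy) defines the outcome as each receipt's percentage of food and beverage dollars spent on discretionary products. It plans a linear mixed model and reports the effect as a percent difference relative to control.

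**The concern.** The outcome is itself a percentage, so a bare percent sign can mean points on that scale or a fraction of the mean. The SD is called relative. The difference is called 8%, but its two endpoints lie 8 percentage points apart, which is 8/50 = 16% in relative terms. At a control mean of 50%, confusing the two scales changes a quantity by exactly a factor of two.

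This sentence is the stated justification for the size of the survey that serves the second study aim. If one quantity is on the wrong scale, a reader cannot tell whether the survey was designed to detect 4 or 8 points. Anyone reusing the printed inputs for a similar survey would get a sample about a quarter of the size, or would carry forward an SD that is half or twice the intended one.

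**Working it through.** **Inputs** (Customer Response, unless noted)
- N = 1080, split 1:1 (Design), so 540 per arm.
- ICC 0.01 and cluster size 45. Design effect = 1 + (45 − 1) × 0.01 = 1.44; the article prints 1.4. Both are used below.
- Relative SD 40%. Taken literally at the control mean: 0.40 × 50 = 20 points.
- Difference: 50 − 42 = 8 points.
- Alpha .05. Sidedness is not stated; two-sided is assumed.

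**Formula.** Effective n per arm = 1080 / design effect / 2, which is 375 (design effect 1.44) or 385.7 (1.4). With d = difference / SD, power ≈ Φ(d × √(n/2) − 1.960).

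**As printed.** d = 8/20 = 0.40.
- Design effect 1.44: 0.40 × √187.5 = 5.48; Φ(5.48 − 1.96) = 99.98%.
- Design effect 1.4: also 99.98%.
- On these inputs, about 277 to 285 customers would give 80% power.

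**Recovering the stated 80%.** d = 0.20.
- Design effect 1.44: 0.20 × √187.5 = 2.74; Φ(2.74 − 1.96) = 78.2%.
- Design effect 1.4: 79.3%.

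Two simple readings give d = 0.20:

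| Reading | Difference | SD | Power | Detectable at 80% power |
|---|---|---|---|---|
| As printed | 8 points | 20 points | 99.98% | 4.0 to 4.1 points |
| (a) Both relative | 8% of 50 = 4 points | 40% of 50 = 20 points | 78.2% to 79.3% | 4.0 to 4.1 points |
| (b) Both absolute | 8 points | 40 points | 78.2% to 79.3% | 8.1 to 8.2 points |

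The last column is (1.960 + 0.842) × SD × √(2/n). For SD 20 and n = 375 it is 2.80 × 20 × 0.0730 = 4.09. Solved the other way, 80% power for 8 points implies an SD of 39.1 to 39.7 points, about twice the literal 20.

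**Other readings of the printed inputs**
- One-sided alpha, an SD taken from the mean of the two arms or from each arm separately, the log scale, or a t reference with 22 degrees of freedom for 24 clusters: power stays above 99.9% in every case.
- A comparison of two proportions, 50% against 42%: 59% to 61%, or 75% without the design effect.
- Keeping SD 20 and 8 points, 80% power would need a design effect of about 5.5, that is (5.45 − 1)/44, or an ICC of about 0.10, against the stated 0.01.

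None of these gives 80%.

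**The case against.** The strongest reply is that no number need be wrong. The outcome is a percentage, and the authors may have meant an SD of 40 on that scale, with the word relative used loosely. Then 40, 50, 42, 1080 and 80% all agree to rounding. Such an SD is possible: for a share bounded by 0 and 100 with mean 50, the largest SD is √(50 × 50) = 50 points. This stands as a possibility, but it is reading (b) and it still requires a printed word to be wrong. The plan to report the effect relative to control sits more easily with reading (a), without deciding the matter.

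It is also fair to say that the consequences are limited. The survey is a substudy on a convenience sample, and the primary outcome has its own precision argument. Under either repair 1080 customers stands. The survey was scheduled for the last two weeks of an intervention that ended in December 2018, so a correction now affects reporting and not the design. Once there are data, a null result should be read from the estimate and its confidence interval, not from the planning SD. These points are accepted. They lower the severity but do not make the sentence correct.

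**Conclusion.** The concern holds. The printed inputs give 99.98% power, not 80%. The stated figure is recovered if the SD is doubled to 40 points or the difference is halved to 4 points, and the document does not say which was intended. The planned detectable difference is therefore ambiguous by a factor of two: about 4.1 or about 8.2 points at a design effect of 1.44.

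This rests on a two-sided alpha, equal arms, a normal approximation and the usual meaning of relative SD as SD divided by mean. The alternatives tried do not change the conclusion. It is an inconsistency in a stated calculation, not evidence that the survey is underpowered, and I rate it moderate.

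**What to change.** Check which SD went into the calculation and restate the sentence on one scale. Either:
- an 8% relative difference (from 50% to 46%) with a relative SD of 40%, that is 20 percentage points; or
- an 8-point difference (from 50% to 42%) with an SD of 40 percentage points, dropping the word relative.

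State that alpha is two-sided, if it is. The per-receipt shares collected in the survey will show which SD is closer to the truth, and that observed SD should be reported beside the planning value.

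A separate matter is worth settling in the same edit. The calculation assumes 24 communities, but Results reports 20 stores randomized. At 45 customers per store that is 900 customers, or 312.5 per arm after the 1.44 design effect. The detectable difference becomes 2.80 × SD × √(2/312.5) = 4.5 points (SD 20) or 9.0 points (SD 40).

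The cost is a one-line correction. Nothing in the design, data collection or analysis model changes.

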## Results

As of August 2018, 20 stores consented to participate and were randomized to receive the intervention or continue usual practice. The 12-week strategy ended in December 2018. The 24-week postintervention follow-up will occur in May 2019. Results are expected for 2019.

## Discussion

### Principal Findings

There is strong evidence to show that merchandising is used to drive sales of discretionary foods [41]. The paucity of evidence on how to use merchandising techniques to reduce purchasing of discretionary products and nudge consumers toward healthier defaults is a large gap in our knowledge [42,43]. The limited available evidence suggests promise in reducing merchandising activity to restrict discretionary products and using merchandising activities to increase visibility and boost sales of targeted core foods [16]. Interest from retailers, including remote community store directors, to engage with researchers represents a unique and invaluable opportunity to address this evidence gap and cocreate knowledge. This trial will provide practical evidence needed to advance how public health can work with retailers to promote, implement, and evaluate health-enabling strategies in this private sector setting. As remote retailers’ decisions directly impact population diet, generating this evidence through collaboration with retailers and other important knowledge users will ensure its viability.

The outcomes will indicate the level of effectiveness and feasibility of the proposed strategy and identify reasons for these outcomes. We will then build on these results to make recommendations for policy, if appropriate, or for the next research study, to identify effective and feasible healthy retailing interventions. The evidence from this study will directly inform the nutrition policy of ALPA and will indirectly influence policies of other retail organizations and community stores through the leadership and influence of ALPA in remote retailing and through the broader effort of the Commonwealth Department of PM&C, which is responsible for food security in remote Indigenous Australia.

### Implications

Comprehensive multicomponent interventions are necessary to improve the quality of the customer food environment [44,45]. Our research will increase the health sector’s understanding of merchandising as a critical factor influencing behavior, one that with appropriate support, can be implemented by retailers. It will also help improve other food environment interventions led by practitioners and academics worldwide, particularly those in other remote populations who experience similar health disparities. Indigenous Australians, especially those who live in remote locations, experience substantially more preventable chronic diseases compared with other Australians. Improving diet is imperative for closing the Indigenous health gap, and improving dietary intake can benefit the future health of generations to come. A key contributor to the adverse diet quality in this population is the alarmingly high intake of the discretionary products that have proliferated the shelves in remote stores [28]. Food is predominantly sourced from community food retail stores, and many retail outlets operating in remote Australia are entirely community owned with store owners seeking in-store solutions to support healthier diets and combat diet-related diseases in a sustained way without negatively impacting on store sales. It is imperative that we work with retailers to provide high quality evidence to inform effective policy and practice for better health outcomes.

### Conclusions

Examining the impact of modifying retail food environments for improved diet and health outcomes is a rapidly expanding research area worldwide [41]. Globally, our team is one of only several research teams who is actively investigating the role of retail food environments in population health. The bringing together of decision makers and practitioners in health and retail sectors including ALPA personnel, with investigators to lead this research, who are involved in food retail environment research in urban, rural, and remote contexts in Australia and Canada, will help lessen the current issue of methodological heterogeneity in the measurement of food environment exposures and outcomes [12,46]. This will enable enhanced generalizability of accumulated evidence on the impact of retail food environments on diet into the future.

## Appendix

Multimedia Appendix 1 Peer review from funding agency.

Multimedia Appendix 2 Authors response to peer review.

## Abbreviations

ALPA: Arnhem Land Progress Aboriginal Corporation
MJ: megajoule
NHMRC: National Health and Medical Research Council
NT: northern territory
PM&C: Prime Minister and Cabinet
SHOP@RIC: stores healthy options project in remote indigenous communities
